## 9.9 Pharmacodynamics endpoints

The analysis of part A and part B will be done separately. The measurements of the afternoon after normal sleep will not be used for the primary analysis. The repeatability of the parameters measured during morning and during the afternoon after normal sleep will be assessed separately on the subset of the after normal sleep data.

The final analysis will be preceded by a data review which consists of individual graphs per visit by time of all pharmacodynamic measurements by time. The graphs will be used to detect outliers and measurements unsuitable for analysis.

The PD parameters will be listed by subject, group (sleep/sleep deprivation), visit and time. Individual graphs by visit/time will be generated.

All PD endpoints will be summarised (n, mean, SD, SEM, median, Min and Max values) by group (sleep/sleep deprivation), and will be presented graphically per group/time in bar graphs with standard deviation as error bars.

Parameters will initially be analysed without transformation, but if the data suggest otherwise, log-transformation may be applied. Log-transformed parameters will be back-transformed after analysis where the results may be interpreted as percentage change.

To estimate the differences between groups (sleep deprived/sleep) data will be analysed with a mixed model analysis of variance with fixed factor group and random factor subject. The contrast sleep vs sleep deprived will be calculated within the model.

To estimate inter- and intra-subject variability the subset data of the sleep group will be analysed with a mixed model analysis of variance with fixed factor time (morning/afternoon) and random factor subject. The variances will be estimated within the model.

The Kenward-Roger approximation will be used to estimate denominator degrees of freedom and model parameters will be estimated using the restricted maximum likelihood method.

Correlations of the change between sleep and sleep deprived values between the cognitive tests, simulated and on-the-road driving will be calculated.

The intra-subject variabilities will be reported as coefficient of variation (CV).

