### **1.2.3 Study design**

An exploratory single-centre cross-over study in healthy subjects. There is no blinding included because of the nature of the study design. Subjects will be randomized on the order of sleep and sleep deprivation.

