#### Design for each part

Subjects will be randomized over the order of study periods, see **Figure 1**. During each study period, participants are admitted to the clinical research unit (CRU). After the measurements in sleep deprived state an interval of at least 5 days is added for recovery.

The measurements will be performed in a standardized order (see **Table 1** for part A and **Table 2** for the measurements of part B).

The total duration of the study for each subject will be up to approximately 50 days for subject who participate in both part A and B.

- Screening: Up to 21 days before first intervention.
- Intervention and study assessments: each study period starts with a urine drug screening and alcohol breath test. Study period 1 (well-rested) starts in the morning upon arrival of the subjects at the CRU. Subjects will perform all assessments twice, in the morning and afternoon. For study period 2 (sleep deprivation), subjects will arrive at the CRU in the evening prior to the study day and stay awake the full night. A single set of the assessments are performed in the morning.

[figure not shown]

Figure 1: Timeline for participants part A or part B

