### 7.1 Efficacy assessments

#### **On-the-road driving test**

Subjects will participate in validated on-road car driving tests. During these tests several safety precautions are taken to guarantee safety of the subjects and regular traffic. A licensed driving instructor (having access to dual controls) guards the safety of the subject and regular traffic during the test. In case the driving instructor or the subject is of the opinion that it is not safe to start or continue the driving test, the test will be interrupted. Subjects will operate a specially instrumented vehicle over a 55-km primary highway circuit, while maintaining a constant speed (95 km/h) and steady lateral position between the delineated boundaries of the right (slower) traffic lane. The subject will be allowed to deviate from this procedure only in order to overtake a slower vehicle traveling in the same traffic lane. The vehicle's speed and lateral position relative to the lane-lines is continuously recorded. These parameters are digitally sampled at 13 Hz by the MobilEye system (MobilEye Vision Technologies Ltd., Israel). Data is edited, off-line, to remove parts where data are disturbed by extraneous events (eg, passing maneuvers). SDLP (cm), ie, the weaving of the car, is the primary outcome variable. SDLP has been shown to be a sensitive measure to demonstrate dose-dependent differences from placebo for alcohol and psychoactive drugs including anxiolytics, antihistamines, antidepressants, hypnotics and analgesics, and drugs of abuse [4, 7, 25]. Standard Deviation of speed (SDS, km/h) will be a secondary variable. Mean lateral position (MLP, +/- cm), and mean speed (MS, km/h) are control variables. During screening, subjects will participate in a training driving test to become acquainted with the procedures of the driving test.

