## 9 STATISTICAL METHODOLOGY AND ANALYSES

### 9.1 Statistical analysis plan

All safety and statistical programming is conducted with SAS 9.4 for Windows or newer (SAS Institute Inc., Cary, NC, USA). A Statistical Analysis Plan (SAP) will be written and finalized before the study closure, i.e., database closure. The SAP will provide full details of the analyses, the data displays and the algorithms to be used for data derivations.

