### **10.3.2 Database management and quality control**

All data from paper source will be entered into the Promasys database twice, by two different individuals. A quality control check will be done by CHDR staff on all data entered in the Promasys database, using data entry progress checks and database listings (blind data review). Errors with obvious corrections will be corrected before database lock.

Results of computer (NeuroCart/PainCart/ECG ect.) tests and electronically captured questionnaires, will be sent electronically to CHDR and loaded into the database.

After the database has been declared complete and accurate, the database will be locked. Any changes to the database after that time can only be made by joint written agreement between the investigator and the statistician.

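### Section 9.9 screens outliers on unmasked per-visit graphs that, for most tests, show the sleep state, and does not limit exclusion to technical faults

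*Protocol*

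**What the plan says.** Section 9.9 puts a review step ahead of the final analysis: "a data review which consists of individual graphs per visit by time of all pharmacodynamic measurements by time". Its purpose follows: "The graphs will be used to detect outliers and measurements unsuitable for analysis". No criterion is given for either category, and nothing is said about what the person reviewing may know.

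Section 1.2.3 states: "There is no blinding included because of the nature of the study design". Under Design for each part, the rested period is described by "Subjects will perform all assessments twice, in the morning and afternoon" and the deprived period by "A single set of the assessments are performed in the morning". Tables 1 and 2 show the same layout: 9:00 and 14:00 columns for the rested state, and a 9:00 column only for the deprived state. Section 9.9 leaves the rested afternoon session out of the primary comparison.

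Three further statements bear on the step:
- Section 9.1 says the SAP "will be written and finalized before the study closure, i.e., database closure".
- Section 9.4 defers the account of unused and spurious data to the study report, does not impute, and relies on the mixed model for missing pharmacodynamic values.
- Section 9.5 admits data to the analyses on a judgement of whether they contribute meaningfully to the objectives.

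**The concern.** The study's first goal is to show that these methods detect sleep deprivation. A very high SDLP, a large sway or an unusual pain threshold after a night awake may be the response itself and not a measurement error. If someone who can see the state decides from a plot that such a value does not belong, the choice depends both on the outcome and on the condition being compared.

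That would affect three outputs: the contrast between sleep and sleep deprivation, its standard error, and the correlations of change between tests. Trimming rested values in the same way would lower the intra-subject CV that the repeatability objective reports. The mixed model offers no protection, because a value removed for its size is not missing at random.

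**Working it through.** **1. Can the reviewer see the state?** For a test scheduled in both rested sessions, a per-visit plot against time has two positions for the rested visit and one for the deprived visit. The number of points therefore identifies the state without any label. This is an inference from the plot format and the schedule; the protocol does not say that the plots are labelled by state. It applies to most tests but not all:
- Table 2 gives the Part B questionnaires no 14:00 session, so those plots do not differ in this way.
- Section 7.1 has the KSS completed before and after each driving test, so a simple two-against-one pattern does not describe it.
- For Part B, section 3.1.2 names only the laser and intra-epidermal tests as repeated in the afternoon, while Table 2 also schedules NeuroCart and PainCart then. How far the point reaches in Part B depends on which is followed.

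**2. The plan's own figure (sections 1.2.7 and 9.3).** Inputs for Part A: n = 24, difference 3.88 cm, SD of differences 6.5 cm, paired t-test, two-sided 0.05. The noncentrality is (3.88 / 6.5) × √24 = 2.92 on 23 degrees of freedom, which gives power 0.7997. Part B (2.09 s, SD 3.5 s) gives 0.7999. The stated 0.80 reproduces in both parts.

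**3. Illustration: the highest deprived values are removed and the rested values kept.** Assumptions not in the protocol are normal data, removal of one or two values, and a within-subject correlation ρ between 0.3 and 0.9. The total SD is set so that the SD of differences stays at 6.5 cm: σ = 6.5 / √(2(1 − ρ)), for example 6.5 cm at ρ = 0.5. The contrast is estimated by generalised least squares with a random subject effect and known variances (40,000 runs). Start: 3.88 cm.

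| ρ | one value removed | two values removed |
|---|---|---|
| 0.9 | 3.65 cm (−5.9%) | 3.45 cm (−11.0%) |
| 0.7 | 3.51 cm (−9.5%) | 3.20 cm (−17.4%) |
| 0.5 | 3.47 cm (−10.7%) | 3.11 cm (−19.7%) |
| 0.3 | 3.44 cm (−11.3%) | 3.08 cm (−20.6%) |

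The same exercise for Part B gives −6.1% to −11.0% for one value and −11.3% to −20.3% for two.

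**4. Illustration: the pairs with the largest differences are dropped.** The mean of 24 standard normal differences falls by 0.084 SD without the largest and by 0.156 SD without the two largest.
- One pair: 0.084 × 6.5 = 0.55 cm, and 0.55 / 3.88 = 14%.
- Two pairs: 0.156 × 6.5 = 1.01 cm, and 1.01 / 3.88 = 26%.

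In 100,000 runs the mean contrast was 3.34 and 2.87 cm, and the rejection rate fell from 0.80 to 0.71 and 0.61.

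**5. The other direction.** Dropping the one or two smallest differences raises the contrast to 4.44 or 4.91 cm. With no true effect, dropping one or two pairs from the same end raises the two-sided type I error from 0.05 to about 0.08 or 0.15.

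**6. Selection against plain loss.** Losing one or two pairs for reasons unrelated to outcome leaves the contrast unbiased and lowers power only to 0.78 or 0.76. The harm in steps 3 to 5 comes from selection.

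**The case against.** The strongest reply is that outlier rules and data displays are ordinary SAP content, that section 9.1 promises full detail there, and that the SAP is not shown. It may well hold an objective rule. The trial also calls itself exploratory. Both points stand and lower the stakes. But the protocol itself has already chosen the procedure, a visual review per visit before the final analysis in an unblinded study, and that choice can be judged as written.

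Second, the text speaks of detecting outliers and not of deleting them. That is true. Exclusion is inferred from the reference to measurements not fit to analyse and from section 9.4's category of unused data.

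Third, the illustrations assume removal at one end only. Removing whichever value lies furthest from the mean, on either side, gives no expected shift for symmetric data. That is also correct, and it is why no direction can be claimed.

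A reader might infer more than the documents support:
- *That section 10.3.2 promises a blind review which 9.9 breaks.* The review named there is quality control of entered data and listings. It is a different procedure, so there is no contradiction, though it does not protect the graph review either.
- *That driving data are trimmed by the same judgement.* Section 7.1 says "Data is edited, off-line, to remove parts where data are disturbed by extraneous events" and gives passing manoeuvres as the example. That is an event-based rule, not removal by size.
- *That the SAP will be final only at database closure.* Closure is the latest permitted date.
- *That exclusions will fall mainly on deprived values, or could never be undone.* Nothing in the protocol supports the first. The second fails because pharmacodynamic values are listed by subject and visit, so flagged values can be restored and the analysis rerun. The protocol simply does not commit to doing so.
- *That the choice of log scale is part of the same fault.* Section 9.9 fixes the untransformed scale as the default, and the rest is normal SAP detail.

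**Conclusion.** The point holds in a limited form. Section 9.9 sets up an outlier review that, for most tests, shows the sleep state, with no masking and no restriction to technical or procedural faults. It acts on the comparison the trial is built around. State-aware exclusion may therefore bias that contrast either way and understate variability.

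The size is illustrative and not a forecast. For Part A SDLP it is about 6-11% for one removed deprived value and 11-21% for two under the mixed model, and 14% or 26% when the pairs with the largest differences are dropped. These figures rest on normality, one-directional removal, an assumed number of exclusions and, for the mixed-model range, an assumed correlation of 0.9 to 0.3. The sample size and the stated power are unaffected. The change should be made because it is cheap and the exposed quantity is the main contrast; it is not a reason to doubt the design.

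**What to change.** Amend section 9.9 so that, for the sleep versus sleep-deprived comparison:

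1. Outlier review uses morning values only, with state and visit labels removed and the order scrambled.
2. A value is excluded only for a documented technical or procedural fault, never for size alone.
3. These criteria are set before the first review graph is made.
4. Every exclusion is logged with its reason.
5. The contrast is reported with and without the exclusions.

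The cost is relabelling the review files, fixing the criteria earlier and one additional run of the model. No new data are needed. The downside is that some implausible but unexplained values stay in the main analysis.

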### **3.1.2 Intervention and observation period**

Subjects will undergo a urine drug screening and alcohol breath test on each arrival at the CRU. During one night per study period they will be deprived from sleep. The subjects will receive standardized meals and non-caffeinated drinks.

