### 9.3 Power calculation

#### Part A

For this power calculation we used aggregated data from a previous CHDR study (CHDR1429) in order to calculate the intra- and inter- SD. The variabilities are based on the change from SDLP values.

For a simulator driving test, a sample size of 24 will have a power of 0.80 to detect a difference in means of 3.88 cm, assuming a standard deviation of differences of 6.5 cm, using a paired t-test with a 0.05 two-sided significance level.

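### The order of the two states is randomised, but neither the fixed analysis model nor the change-score correlations account for visit order

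*Protocol*

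**What the plan says.** Section 1.2.3 states: "Subjects will be randomized on the order of sleep and sleep deprivation". Section 3.1 (Design for each part) repeats it: "Subjects will be randomized over the order of study periods". For the comparison of states, section 9.9 says that "data will be analysed with a mixed model analysis of variance with fixed factor group and random factor subject". It then takes the sleep versus sleep-deprived contrast from that model, using REML and Kenward-Roger degrees of freedom. No period, visit-order or sequence term appears in section 9. Visit is used there only for listings and graphs, and the time factor in the separate repeatability model is morning versus afternoon.

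For the relationship between tests, section 9.9 says: "Correlations of the change between sleep and sleep deprived values between the cognitive tests, simulated and on-the-road driving will be calculated". It mentions no adjustment for order.

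Section 9.3 gives the Part A power statement: "a sample size of 24 will have a power of 0.80 to detect a difference in means of 3.88 cm". Its inputs are an SD of 6.5 cm for the within-subject differences and a two-sided paired t-test at the 5% level. Part B uses 2.09 s and an SD of 3.5 s with the same n, power and test.

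**The concern.** Randomising order lets a change common to everyone between the first and second visit be separated from the effect of sleep deprivation. A model with group as its only fixed factor does not use this. Any visit-order effect enters each subject's deprived-minus-rested difference with a plus sign in one order and a minus sign in the other.

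There are three possible consequences. With balanced orders the extra spread enters the residual, which loses power and makes the test conservative. With unequal realised orders the two signs do not cancel and the contrast moves. For the correlations, two tests that both have a visit-order effect have changes that rise and fall together by order, even if they are otherwise unrelated. This last point bears on the third Part A objective in section 2, the relationship between road driving, simulated driving and NeuroCart performance. Balance does not remove it.

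**Working it through.** **Inputs.** From section 9.3: n = 24; Part A difference 3.88 cm, SD of differences 6.5 cm; Part B 2.09 s, SD 3.5 s; two-sided 0.05. Assumed: the visit-order shift π (second visit minus first) and any split other than 12/12. The documents give neither.

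**Plan's own figure.** With complete pairs, the group plus random subject model is equivalent to the paired t-test. Part A: SE = 6.5/√24 = 1.327, noncentrality 3.88/1.327 = 2.92, 23 df, power 0.7997. Part B gives 0.7999. Both reproduce the stated 0.80.

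**Set-up.** Write each subject's difference as D = τ + sπ + e, where s = +1 for rested first and −1 for deprived first, e has SD σ, and f = π/σ.

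**1. Balanced orders, 12/12, no period term.** The residual variance becomes σ² + π²·24/23, so the SD is inflated by √(1 + f²·24/23). Power is from simulation, 100,000 trials per scenario.

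| f | π, Part A | SD inflation | Type I error | Power without term | Power with term |
|---|---|---|---|---|---|
| 0 | 0 | 1.00 | 0.05 | 0.800 | 0.798 |
| 0.25 | 1.6 cm | 1.03 | 0.044 | 0.78 | 0.80 |
| 0.5 | 3.25 cm | 1.12 | 0.029 | 0.72 | 0.80 |
| 1 | 6.5 cm | 1.43 | 0.006 | 0.50 | 0.80 |

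With the term, the estimate is the mean of the two order-specific mean differences, with 22 df and SE = (σ/2)√(1/n1 + 1/n2). At 12/12 this is 3.25 × √(2/12) = 1.327, giving power 0.798 whatever the size of π. Part B gives the same power because 2.09/3.5 and 3.88/6.5 are both 0.597.

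**2. Unequal orders.** The shift in the estimate is π(n1 − n2)/(n1 + n2). At an assumed 14/10 the factor is 4/24.
- Part A: 1.625 × 4/24 = 0.27 cm, 3.25 × 4/24 = 0.54 cm, 6.5 × 4/24 = 1.08 cm, on 3.88 cm.
- Part B, with π = 0.875, 1.75 and 3.5 s: 0.15, 0.29 and 0.58 s, on 2.09 s.

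The direction depends on the sign of π and on which order is larger. With the term the estimate is unbiased for a common shift, and power at 14/10 is 0.787. No allocation ratio or blocking is stated. If order were assigned by simple randomisation (an assumption), an exact 12/12 split would have probability 0.16 and a difference of 4 or more would have probability 0.54.

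**3. Correlations.** Two changes with true correlation 0 and scaled shifts f1 and f2 acquire r = f1·f2/√((1 + f1²)(1 + f2²)). With f1 = f2 = 0.25, 0.5 and 1 this is 0.0625/1.0625 = 0.06, 0.25/1.25 = 0.20 and 1/2 = 0.50. At 12/12, simulation (40,000 trials) made these nominally significant in 6%, 16% and 80% of trials. Adjusting both changes for sequence returned r to about 0 and the rate to about 5%.

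**The case against.** **Size.** The strongest objection is that the larger shifts are implausible. Section 7.1 gives a yardstick on the same simulator: alcohol at 0.5 g/L changed SDLP by 1.9 cm, alcohol at 1.0 g/L by 3.0 cm and alprazolam 1 mg by 5.6 cm. A 3.25 cm shift from visit order alone exceeds the higher alcohol effect, and 6.5 cm exceeds alprazolam. Subjects practise at screening, Part A recruits experienced drivers, and section 7.1 calls learning on adaptive tracking limited after three practice sessions. At an assumed 1 cm, power at 12/12 is 0.79, bias at 14/10 is 1 × 4/24 = 0.17 cm and spurious r is 0.02. This stands, and the small-shift rows should carry the weight. Limited is not nil, however, and that statement covers one test.

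**Bias.** A reader might infer that the contrast is biased as planned. It is not at 12/12. Averaged over simple randomisation, simulated mean estimates stayed at about 3.87 to 3.88 cm and type I error at about 0.05. The bias is conditional on the realised split. A systematic bias would need losses related to order, and nothing in the protocol indicates them. Discretionary replacement (section 4.6.3) and the exclusion of short road tests (section 9.4) only make imbalance possible.

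**Labels.** The schedule names the rested state as period 1 ("Study period 1 (well-rested) starts in the morning upon arrival of the subjects at the CRU") and the deprived state as period 2. A reader might infer that visit order and state cannot be told apart in the data. The documents do not support this: the notes to Tables 1 and 2 say that order is randomised, and section 9.9 lists data by group and by visit separately.

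**Status.** The study is exploratory, and section 9.1 leaves full analysis details to the SAP. That limits severity but does not remove the point, because section 9.9 itself names the model's terms.

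**Conclusion.** The point holds as a conditional one. The protocol fixes a model that omits visit order in a design that randomises it, and it plans correlations that ignore it. Harm follows only if a period effect remains after training, and for the correlations only if both endpoints have one. Over the assumed range of 0.25 to 1 SD, power at 12/12 runs from 0.78 down to 0.50, bias at 14/10 from 0.27 to 1.08 cm, and spurious r from 0.06 to 0.50. The lower end is the more credible. The sample-size figures themselves are correct; whether the historical SD already contains some period variation is not stated. This should be fixed because the remedy is standard and nearly free, but an exploratory study does not stand or fall by it.

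**What to change.** In both parts, add period as a fixed factor to the group plus random subject model. Code it from the actual visit order, first or second, and not from the Study period 1 and 2 labels. Those labels denote the states, so a factor built from them would be aliased with group.

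Compute the change-score correlations as partial correlations adjusted for sequence. The period term in the mixed model does not repair them.

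The cost is wording and one degree of freedom: power 0.800 to 0.798 at 12/12 if there is no period effect. Section 10.6.2 already treats changed statistical analyses as non-substantial amendments.

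One limit remains. The rested visit has two test sessions and the deprived visit one, so practice before the second visit differs by order. A period term removes only the part of the effect common to both orders.

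Separately, and as an editorial matter, section 3.1.2 says: "During one night per study period they will be deprived from sleep". Section 3.1 describes one rested and one deprived period. These passages and the schedule labels must be reconciled.

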### Part B

- To assess the effect of sleep deprivation on event related potentials and EEG
- To assess the effect of sleep deprivation on pain tolerance / pain detection threshold using the PainCart, a pain test battery;
- To investigate the effect of sleep deprivation on IES sensitivity and LEPs;
- To estimate the repeatability of IES and LEP at day time at two different time points after a regular night of sleep.

Table 1. Visit and Assessment Schedule – Part A

| Time point
Assessment           | SCR
Up to -21 d                                                                 | Study Part A                                     |                   |                                                     |
|------------------------------------|------------------------------------------------------------------------------------|--------------------------------------------------|-------------------|-----------------------------------------------------|
|                                    |                                                                                    | Study period 1
Well rested state  |                   | Study period 2
Sleep deprived state  |
| Projected start time assessments   |                                                                                    | Start at 9:00 hr                                 | Start at 14:00 hr | Start at 9:00 hr                                    |
| Informed consent                   | X                                                                                  |                                                  |                   |                                                     |
| Demographics                       | X                                                                                  |                                                  |                   |                                                     |
| In- and exclusion criteria         | X                                                                                  |                                                  |                   |                                                     |
| Physical examination               | X                                                                                  |                                                  |                   |                                                     |

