#### **NeuroCart**

- Adaptive tracking. Average performance on adaptive tracking CFB (%).
- Body Sway. Total antero-posterior sway (mm).
- Eye movements. percentage time the subjects eyes are in smooth pursuit of the target during smooth pursuit
- VAS Bond and Lader. Composite scores for alertness (mm).

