#### **EEG**

- Resting-EEG. Frequency band power (Hz).
- EEG in combination with auditory steady-state response. The average inter-trial phase coherence between 35 and 45 Hz and between 200 and 500 ms. The average evoked power between 35 and 45 Hz and between 200 and 500 ms.
- EEG in combination with Oddball tasks. P300 and MMN amplitudes ( $\mu$ V) and latencies (msec).
- EEG in combination with visual evoked potentials (VEP). N75 and P100 amplitudes ( $\mu$ V) and latencies (msec).

- EEG in combination with laser-evoked potentials (LEP). Amplitude ( $\mu\text{V}$ ) and latency (ms) of LEPs (N2, P2, and N2P2).

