**PainCart**

- Heat Pain: Pain Detection Threshold (PDT) ( $^{\circ}\text{C}$ )
- Electrical Burst: PDT (mA), Pain Tolerance Threshold (PTT) (mA), Area Under the VAS pain Curve (AUC) ( $\text{mA}\cdot\text{mm}$ ), and post-test VAS (mm).
- Electrical Stair (pre-cold pressor): PDT (mA), PTT (mA), Area Under the VAS pain Curve (AUC) ( $\text{mA}\cdot\text{mm}$ ), and post-test VAS (mm).
- Electrical Stair (post-cold pressor): PDT (mA), PTT (mA), AUC ( $\text{mA}\cdot\text{mm}$ ), and post-test VAS (mm).
- Conditioned Pain Modulation Response (change from electrical stair pre- and post-cold pressor): PDT (mA), PTT (mA), AUC ( $\text{mA}\cdot\text{mm}$ ).
- Pressure Pain: PDT (kPa), PTT (kPa), AUC ( $\text{kPa}\cdot\text{mm}$ ), and post-test VAS (mm).
- Cold Pressor: PDT (s), PTT (s), Area Above the VAS pain Curve (AAC) ( $\text{s}\cdot\text{mm}$ ), and post-test VAS (mm).
- Laser-evoked potentials: Subjective pain perception after LS (LS-NRS): Numeric rating scale (0-10 with 0=no pain & 10=worst pain imaginable).
- McGill Pain Questionnaire for each individual test.

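### Section 9.9 fixes the CV as the only reported intra-subject measure, which does not describe repeatability for the change-score, arbitrary-origin and near-zero signed endpoints among those measured twice

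*Protocol*

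**What the plan says.** Section 9.9 sets up a repeatability analysis: "The repeatability of the parameters measured during morning and during the afternoon after normal sleep will be assessed separately" on the normal-sleep data. Those data are to be "analysed with a mixed model analysis of variance with fixed factor time (morning/afternoon) and random factor subject", and "The variances will be estimated within the model". The section closes with the reporting rule: "The intra-subject variabilities will be reported as coefficient of variation (CV"). It gives no formula, no exception and no alternative measure. Analysis is untransformed by default, with a log transformation allowed if the data suggest it.

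The repeatability objectives in section 2 name SDLP, on road and simulated, for Part A. For Part B the aim is "To estimate the repeatability of IES and LEP at day time". The analysis in 9.9 is wider than these objectives, because it covers whatever is measured both morning and afternoon.

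Section 6.2 lists these endpoints, among others:
- LEP amplitude and latency "of LEPs (N2, P2, and N2P2");
- "Conditioned Pain Modulation Response (change from electrical stair pre- and post-cold pressor"), for detection threshold, tolerance threshold and area under the curve;
- "Average performance on adaptive tracking CFB" in per cent;
- heat pain detection threshold in °C;
- the Karolinska Sleepiness Scale (KSS) and perceived driving quality.

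The protocol gives differing accounts of what is repeated in Part B. Section 3.1 has all assessments done twice in the well-rested period. Table 2 marks NeuroCart and PainCart at 14:00 but not the questionnaires. Section 3.1.2 names only laser stimulation and intra-epidermal stimulation for the repeat. In Part A, section 3.1.2 and Table 1 agree that the tests, questionnaires and subjective driving assessment are repeated.

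**The concern.** With untransformed analysis, the CV is the within-subject SD divided by the mean. The numerator measures repeatability. The denominator is a useful yardstick only if zero means absence of the quantity and the mean is not close to zero. Several endpoints in the morning/afternoon model lack one or both properties. For them the reported figure can change with the origin of the scale, take either sign, or become very large, while the precision of the test stays the same.

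The study aims to validate these methods for later use, and repeatability is an objective of both parts. A reader will set the CVs side by side to judge which tests are most repeatable. For the affected endpoints, that ranking would partly reflect where zero lies on the scale.

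**Working it through.** **The plan's own figures.** The protocol states no CV, so there is none to reproduce. Its computable figures are the powers in section 9.3 (paired t-test, n = 24, two-sided 0.05), and these do not use a CV. The noncentrality is (difference / SD of differences) × √24:
- Part A: 3.88/6.5 × 4.899 = 2.924, power 0.7997.
- Part B: 2.09/3.5 × 4.899 = 2.925, power 0.7999.

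Both agree with the stated 0.80.

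**Which endpoints are in the model.**
- On every reading: all Part A tests, including adaptive tracking, KSS and perceived driving quality; and IES and LEP in Part B.
- Only if section 3.1 and Table 2 hold: heat threshold and conditioned pain modulation.
- Not in Part B, going by Table 2: the questionnaires.

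The protocol gives no means or within-subject SDs for the affected endpoints, so every mean and SD below is assumed. CV = within-subject SD / mean throughout.

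**Arbitrary origin: heat threshold.** Assume mean 44 °C and SD 1 °C. The 32 °C starting temperature is from section 7.1.

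| Scale | Calculation | CV |
|---|---|---|
| °C | 1/44 | 2.27% |
| °F | 1.8/111.2 | 1.62% |
| Rise above 32 °C | 1/12 | 8.33% |

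The ratio of the third CV to the first is mean/(mean − 32), whatever the SD: 40/8 = 5.0, 44/12 = 3.7 and 48/16 = 3.0 for means of 40, 44 and 48 °C.

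**Arbitrary origin: KSS (1 to 9).** Assume mean 3 and SD 1. The CV is 1/3 = 33%. Scored 0 to 8, the same answers give 1/2 = 50%. Perceived driving quality (0 to 20, with normal driving at the midpoint) has the same property.

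**Change score: conditioned pain modulation.** Assume SD 1 mA.

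| Mean change (mA) | CV |
|---|---|
| 2 | 50% |
| 1 | 100% |
| 0.5 | 200% |
| 0.1 | 1000% |
| 0 | undefined |
| −0.1 | −1000% |

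Adaptive tracking behaves in the same way if CFB is a change from baseline with a well-rested mean near zero.

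**Signed endpoint: LEP N2 amplitude.** Simulated with n = 24, between-subject SD 3 µV and within-subject SD 2 µV. The negative sign is inferred from the name of the peak; the protocol states no sign convention.

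| Mean (µV) | True CV | 95% range of estimates | Share of values ≥ 0 |
|---|---|---|---|
| −12 | −17% | −22% to −12% | 0% |
| −8 | −25% | −34% to −18% | 1% |
| −4 | −50% | −79% to −32% | 13% |
| −2 | −100% | −285% to −53% | 29% |

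With a within-subject SD of 4 µV, the true CV runs from −33% at a mean of −12 µV to −200% at −2 µV.

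**The log option does not rescue these endpoints.** A log cannot be taken of zero or negative values, which rules out change scores and a negative N2. For degrees Celsius or KSS, a log transformation still depends on where zero was placed.

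**The case against.** The strongest reply has five parts.

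- **Scope.** A reader might infer that the CV is imposed on every endpoint. Section 9.9 confines the analysis to parameters measured morning and afternoon, and section 3.1.2 would confine Part B to laser and IES. This stands: the heat and pain-modulation examples are conditional on the afternoon PainCart.
- **N2.** A reader might infer that the CV is undefined for N2 and that the LEP repeatability objective therefore fails. It does not. With a mean well away from zero the CV is merely negative, and SD/|mean| is usable. The protocol gives no N2 mean that would show a problem. This stands, and N2 is the weakest example.
- **Tracking.** Section 6.2 lists CFB, which the abbreviation list does not define, while section 7.1 says average performance and its SD are analysed. If performance itself is the variable, the change-score objection falls away. This stands as a condition.
- **Fixed units.** Heat threshold is reported in °C only, so its CV is reproducible and can be compared with other results in °C. True, but the CV still cannot be set against the CV of another test, and within-study comparison across tests is where it would be read.
- **Left to the SAP.** Section 9.1 leaves algorithms to the SAP, which could set a formula. It could, but the protocol has already named the measure without qualification, and for these endpoints it is the measure that is unsuitable.

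A reader might also infer that later trials could not be sized from the results. The documents do not support that: the model estimates the intra-subject variance, and section 9.3 works from an SD of differences, not a CV.

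**Conclusion.** The point holds in a limited form. As an unqualified rule, the CV sentence suits SDLP, IES thresholds, reaction times, latencies and peak-to-peak N2P2. It does not suit the change scores and arbitrary-origin scales among the endpoints measured twice, or N2 if its mean is near zero.

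The size of the distortion rests on assumed values: a factor of 3 to 5 for heat threshold depending on the origin used, and no upper bound for a change score as its mean approaches zero.

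KSS and perceived driving quality are affected on any reading of the schedule. Heat threshold and conditioned pain modulation are affected only if PainCart is repeated in the afternoon, and tracking only if CFB is a change from baseline.

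The consequence is confined to the descriptive repeatability results. The sleep versus sleep-deprived contrast uses neither the CV nor the afternoon data, and the sample size is untouched.

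**What to change.** Replace the CV sentence in section 9.9 with: *Intra-subject variability will be reported as the within-subject SD in original units, from the planned mixed model, for all endpoints measured morning and afternoon; a CV will be given in addition only for strictly positive ratio-scale endpoints.*

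Two related points need settling so that the list of affected endpoints is known. Section 3.1, section 3.1.2 (Part B) and Table 2 must be reconciled on which Part B tests are repeated. Sections 6.2 and 7.1 must be reconciled on which adaptive tracking variable is analysed.

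The within-subject SD is the square root of a variance that the model already estimates, so no new data or model is needed. The only cost is slightly more output.
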